(1) Population-based	Mortality, general practitioner visits, community-nurse visits, cumulative days per year admitted in hospital, emergency department visits, all hospital admissions, potentially avoidable hospitalizations, multiple drug prescription, needs for social support, costs per patient per year (Additional file 1: Table S1)		A. What are the possible factors and agents responsible for good implementation of a health intervention? B. What are the possible factors for enhancing or expanding a given health intervention? C. What describes the context in which implementation occurs? D. What describes the main factors influencing implementation in a given context? To be assessed using a mixed methods approach: combining qualitative and quantitative methods	Assessment of the twelve dimensions of the Maturity Model for Integrated Care, both at health system and health services levels, promoted by the European Innovation Partnership for Active and Healthy Ageing, following the instructions reported in reference (4). These twelve dimensions are: 1. Readiness to Change 2. Structure & Governance 3. Information & eHealth Services 4.Standardization& Simplification 5. Finance & Funding 6. Removal of Inhibitors 7. Population Approach 8. Citizen Empowerment 9. Evaluation Methods 10. Breadth of Ambition 11. Innovation Management 12. Capacity Building
(2) Home hospitalization	Health and well-being	Mortality rate 30/90 days after discharge, place of death, avoidable hospital admissions, total bed days, 12 months before admission (hospital and community resources); 30-day after discharge (hospital and community resources), transitional care strategies (palliative care, primary care or hospital care)		
	Patient experience	Person centeredness, continuity of care (Additional file 2: Table S2)		
	Costs	Operational costs		
(3) Prehabilitation	Health and well-being	Cumulative hospital days of stay, intensive care unit length of stay, number of complications per patient, costs from the perspective of the hospital including inpatient services, diagnostic procedures, pharmaceutical consumption and blood products consumption, aerobic capacity, physical activity, psychological status, health status (Additional file 3: Table S3)		
	Costs	Operational costs		

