The assessment protocols will combine three different data sources. First, registry data obtained from the Catalan Health Surveillance System (CHSS) [16, 39, 40], as briefly described below. Second, individual data extracted from the electronic healthcare records from primary care and specialized care. Third, data derived from prospectively applied standardized questionnaires to patients, health professionals and managers (Additional file 1: Table S1, Additional file 2: Table S2, Additional file 3: Table S3 and Additional file 4: Table S4). The challenges involved in the combination of different datasets used in these four assessment protocols have been overcome within the framework of the recent EU General Data Protection Regulation (GDPR) [41].

The CHSS includes updated registries from primary care, hospital-related events (e.g. hospitalization, emergency room and specialized outpatient visits), pharmacy, mental health, socio-sanitary services, respiratory therapies, dialysis, outpatient rehabilitation and non-urgent transport of all citizens living in Catalonia (7.5 M) since 2011. The information is updated every 6 months. It provides a basis for cost analyses of the use of healthcare resources, pharmacy consumption, and prevalence of key health problems. The CHSS feeds the regional population-based risk stratification tool named Adjusted Morbidity Groups (GMA) that complies with the following characteristics: i) A population health approach; ii) No licensing constraints; iii) Open source computational algorithms; and, iv) The adjusted morbidity grouper relies mostly on statistical criteria, as opposed to other tools that include expert-based coefficients, thus facilitating quick transferability to other territories [39, 42].

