#### Assessment protocol 2: home hospitalization (HH)

The intervention group to be analysed will include all the patients admitted to HH and early discharge service from HCB during a one-year period (October 2017–October 2018) (*n* = 1146), approximately 70% of the patients were admitted to HH directly from the emergency room. A subset of the patients admitted to HH directly from the emergency room throughout the study period will be assessed separately (*n* = 200).

The characteristics of the intervention have recently been described by Hernandez et al. [13] in terms of implementation strategy, outcomes and costs during the deployment of the service in a real-life setting during the years 2006–2015. During the period 2017–2018, the programme was expanded to 48 beds per day to cover the entire AISBE health district.

The principal objective of this protocol is to assess hospital avoidance and early hospital discharge at health district level. Moreover, the approach aims to generate recommendations for shared-care agreements between specialized and community-based care after discharge to ensure safe transitional care strategies.

The assessment protocol will consist of a prospective controlled cohort study wherein patients admitted to HH directly from the emergency room (intervention) (*n* = 800) will be compared with conventional hospitalisation (control) (*n* = 800). The control group will include patients admitted to conventional hospitalization directly from the emergency room of the same hospital (HCB). PSM will be used for comparability purposes using age, sex, GMA, socioeconomic status, number of hospitalisations during the previous year and polypharmacy as matching variables. As described above, a sub-group of 200 consecutive patients recruited on a voluntary basis, admitted through the emergency department during the study period, from each arm (HH and conventional hospitalization) will be also thoroughly characterized using a set of standardized questionnaires [26, 27, 30], as depicted in Tables 2 and Additional file 2: Table S2. It is of note that these two well defined sub-groups of 200 patients each (*n* = 400) will also constitute a single fixed cohort for later analysis on the interactions between specialized and community-based care using network and cluster analyses alongside qualitative methodologies.

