#### Assessment protocol 3: Prehabilitation service

This is a preventive intervention targeted at high risk candidates for major surgical procedures carried out preoperatively aiming at reducing complications and enhancing postoperative recovery. It combines: i) Motivational interviewing; ii) High-intensity endurance exercise training; iii) Promotion of physical activity; iv) Nutritional supplementation; and; v) Psychological support.

The intervention is currently deployed as a mainstream service at HCB in several types of major surgeries. During fall 2017, three multidisciplinary workshops using a design-thinking approach were carried out to refine the service workflow and to explore the potential for service scalability. The outcomes of the co-design process provided a robust background for the design of a future personalized perioperative care service at regional level covering three phases: prehabilitation, in-patient care, and post-discharge rehabilitation.

The current assessment protocol aims to assess cost-effectiveness of prehabilitation as a mainstream service in the ongoing deployment at HCB, as well as to generate a roadmap for regional scalability of the service. It is planned as a prospective controlled cohort study including 500 consecutive patients undertaking prehabilitation, as the intervention group, and patients following standard care before surgery, in the same hospital (i.e. HCB), as the control group (2:1 intervention to control ratio). The patients will be included from the following type of surgeries: major digestive surgery (*n* = 525), lung volume reduction (*n* = 30), radical cystectomy (*n* = 30), major cardiovascular surgery (*n* = 165). Study groups will be made comparable using PSM with the following matching variables: type of surgery, age, sex, American Society of Anaesthesiologists index and GMA grading. Patients’ clinical outcomes will be assessed at baseline, pre-surgery and 30 days after surgery. The primary outcome will be cost-effectiveness, meaning reduced hospital stay and early re-admissions. Secondary outcome variables will include number of complications per patient, healthcare use, aerobic capacity, physical activity and psychological and health status. The specificities of the assessment protocol are summarized in Additional file 3: Table S3.

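### The home hospitalization propensity score uses only pre-admission characteristics, so the emergency-room placement decision that separates the two arms is left unadjusted

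*Protocol article*

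**What the plan says.** The Methods section of the protocol article makes propensity score matching the means by which the arms of all four protocols become comparable, and the Discussion says this approach was chosen in place of randomization. For home hospitalization, the matching is done "using age, sex, GMA, socioeconomic status, number of hospitalisations during the previous year and polypharmacy as matching variables".

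The comparator is defined by where the patient was admitted: "The control group will include patients admitted to conventional hospitalization directly from the emergency room of the same hospital (HCB"). The article states no restriction to patients who could have gone home and no restriction by diagnosis. The intervention arm of 800 "will be compared with conventional hospitalisation (control) (*n* = 800").

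Table 2 lists the Protocol 2 outcomes. They include mortality at 30 and 90 days after discharge, bed days, resource use in the 30 days after discharge, and operational costs. The same cell also contains "total bed days, 12 months before admission (hospital and community resources").

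The prehabilitation protocol uses a different set: "type of surgery, age, sex, American Society of Anaesthesiologists index and GMA grading". The data sources named in the Methods include "individual data extracted from the electronic healthcare records from primary care and specialized care".

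**The concern.** Both arms enter through one emergency room, and what separates them is a decision made at that visit. One would expect the decision to depend on the presenting problem, on how ill the patient is that day, and on whether someone can help at home. These factors also predict death, length of stay and cost, so they are confounders by indication, and the matching list contains none of them.

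The listed variables are weak stand-ins. Age, sex and socioeconomic status are demographic. Previous-year hospitalisations and polypharmacy describe history. GMA is a population morbidity grade fed by a registry that the Methods say is refreshed every six months, so it cannot be expected to reflect acute status on arrival.

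A post-match table balanced on these six variables would look reassuring and would say nothing about the imbalance that matters most. A larger sample would not help, because the bias does not shrink with sample size.

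**Working it through.** **The plan's own figure.** The article describes all home hospitalization and early discharge patients "during a one-year period (October 2017–October 2018) (*n* = 1146") and says that about 70% came directly from the emergency room. 1146 × 0.70 = 802, which agrees with the stated 800. The arm size is thus a service-volume count. The article gives no event rate, effect size or power for this comparison, so the size of any bias has to be illustrated with assumptions.

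**Classifying the matching variables.**
- Demographic or socioeconomic: age, sex, socioeconomic status.
- Prior morbidity and use: GMA, hospitalisations in the previous year, polypharmacy.
- Index admission: none.

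The prehabilitation set contains two variables that describe the index episode, type of surgery and the ASA index. The frail elderly protocol uses the same six variables as home hospitalization, although it also covers long-term case management and geriatric residences. The six are therefore a general set and are not specific to an acute placement decision.

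**Bias from one omitted binary factor.** Let severe acute illness have prevalence p1 in the home arm and p0 in the ward arm after matching. Let it multiply mortality by R, and let the true effect of the service be null. Then

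apparent risk ratio = (1 + p1(R − 1)) / (1 + p0(R − 1)).

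All values of p1, p0 and R below are assumptions:
- p1 = 0.30, p0 = 0.40, R = 2: 1.30 / 1.40 = 0.93
- p1 = 0.20, p0 = 0.40, R = 3: 1.40 / 1.80 = 0.78
- p1 = 0.20, p0 = 0.50, R = 3: 1.40 / 2.00 = 0.70

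**Chance of a falsely significant benefit with 800 per arm.** This takes mortality without severe illness as 3% or 5% (also assumed) and a two-sided 5% test.
- Mild case (3%, R = 2, 30% of ward versus 20% of home patients severe): 3.9% versus 3.6% mortality, risk ratio 0.92, chance 5%.
- Middle case (5%, R = 3, 30% versus 10%): 0.05 × 1.6 = 8.0% versus 0.05 × 1.2 = 6.0%, risk ratio 0.75, chance 35%.
- Extreme case (5%, R = 4, 50% versus 10%): 12.5% versus 6.5%, risk ratio 0.52, chance 98%.
- Severity balanced (20% in both arms): risk ratio 1.00, and the chance returns to the nominal 2.5%.

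**The case against.** The strongest reply is that Additional file 2 (Table S2) is not shown and may hold eligibility criteria. If controls are already limited to patients whom the service would have accepted, part of the severity gap is closed before matching. This stands as a reason to ask for confirmation. It does not remove the point: the article itself fixes the matching list, and eligible patients can still differ in diagnosis and severity.

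It is also fair to say that the documents give neither the placement rule nor the case mix of either arm. A reader might infer that sicker patients demonstrably stay on the ward and that the service will be shown as safer than it is. The documents do not support that as fact. The direction is what emergency-room triage would be expected to produce, and the stated principal objective is hospital avoidance and early discharge. Nor are the six variables all chronic history, since three are demographic.

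Three further readings go too far:
- **Prehabilitation.** A reader might infer the same fault there, because aerobic capacity and psychological status are not matched although "clinical outcomes will be assessed at baseline, pre-surgery and 30 days after surgery". That set already includes type of surgery and the ASA index, and adjustment for baseline values of outcomes is commonly left to the analysis plan.
- **Pre-admission resource use.** A reader might infer that Table 2 treats it as an effect of the service. The entry stands beside a 30-day post-discharge window for the same resources and reads naturally as its baseline.
- **Readmission.** It is not a named outcome for Protocol 2 in Table 2; the 30-day readmission entry belongs to the frail elderly protocol.

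**Conclusion.** The point holds for home hospitalization. As written, the plan relies on matching for comparability, and the matching set contains no variable from the index admission. The stated control definition does not repair this. Residual confounding by indication is likely in 30/90-day mortality, bed days, post-discharge resource use and costs, probably in favour of home hospitalization.

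The size cannot be identified from the documents. An apparent risk ratio of 0.93 to 0.70 under no true effect is an illustration that rests on assumed prevalences and risk ratios, and the wider grid of assumptions runs from 0.92 to 0.52. The milder assumptions do little harm. The middle ones would produce a finding that could be mistaken for a benefit.

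**What to change.** Amend the Protocol 2 matching specification as follows:
- Add the main admission diagnosis group and a measure of acute severity, both as recorded in the emergency room before placement and in the same way for both arms. Values coded at discharge would already reflect the care received. Add home support where the record holds it.
- State whether controls are limited to patients who met the service's existing admission criteria. If they are not, apply that restriction before matching.
- Use the 12-month pre-admission resource use, which is already to be collected, as a baseline covariate in the propensity model, and label it as baseline in Table 2.
- Report post-match balance on the added variables, with a sensitivity analysis for unmeasured confounding.

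The cost is a few more fields from electronic records that are already a named source. The article does not say that severity or home support is recorded there, so availability should be checked first. Some treated patients may find no match. With about 802 direct admissions for a planned 800, there is almost no slack, so the matched number may fall below 800. The analysis should then say which patients the estimate covers.

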#### Assessment protocol 3: Prehabilitation service

This is a preventive intervention targeted at high risk candidates for major surgical procedures carried out preoperatively aiming at reducing complications and enhancing postoperative recovery. It combines: i) Motivational interviewing; ii) High-intensity endurance exercise training; iii) Promotion of physical activity; iv) Nutritional supplementation; and; v) Psychological support.

The intervention is currently deployed as a mainstream service at HCB in several types of major surgeries. During fall 2017, three multidisciplinary workshops using a design-thinking approach were carried out to refine the service workflow and to explore the potential for service scalability. The outcomes of the co-design process provided a robust background for the design of a future personalized perioperative care service at regional level covering three phases: prehabilitation, in-patient care, and post-discharge rehabilitation.

The current assessment protocol aims to assess cost-effectiveness of prehabilitation as a mainstream service in the ongoing deployment at HCB, as well as to generate a roadmap for regional scalability of the service. It is planned as a prospective controlled cohort study including 500 consecutive patients undertaking prehabilitation, as the intervention group, and patients following standard care before surgery, in the same hospital (i.e. HCB), as the control group (2:1 intervention to control ratio). The patients will be included from the following type of surgeries: major digestive surgery (*n* = 525), lung volume reduction (*n* = 30), radical cystectomy (*n* = 30), major cardiovascular surgery (*n* = 165). Study groups will be made comparable using PSM with the following matching variables: type of surgery, age, sex, American Society of Anaesthesiologists index and GMA grading. Patients’ clinical outcomes will be assessed at baseline, pre-surgery and 30 days after surgery. The primary outcome will be cost-effectiveness, meaning reduced hospital stay and early re-admissions. Secondary outcome variables will include number of complications per patient, healthcare use, aerobic capacity, physical activity and psychological and health status. The specificities of the assessment protocol are summarized in Additional file 3: Table S3.

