All of the above factors contribute to explain the difficulties encountered in the process of standardization of IC assessment. Over the past several years, evaluation of well-established IC programs, alongside pilot experiences, has been undertaken in several countries with mixed results [7–9]. Overall, these experiences have contributed to the generation of a series of general recommendations on evaluation of IC with focus on service transferability across geographical sites aimed at fostering regional scalability [4, 10]. It is of note, however, that application of these recommendations for a comprehensive assessment of deployment of IC services in real-life scenarios is clearly an unmet need.

The current manuscript aims to describe a structured evaluation framework (Fig. 1) that articulates four comprehensive assessment protocols covering both vertical and horizontal levels of integration. One assessment protocol reports a population-based assessment of outcomes from past and current Catalan Health Plans, 2011–2015 [11] and 2016–2020 [12], respectively, whereas the other three assessment protocols address the deployment of specific IC services during the period 2017–2018, namely: i) Home hospitalization [13]; ii) Prehabilitation of candidates for major surgery [14]; and, iii) Community-based advanced care service for frail elderly [15, 16]. The ultimate aim of the research is to explore the application of innovative evaluation strategies [4] for IC services deployed in real-life settings. To this end, a comprehensive evaluation of outcomes following a Quadruple Aim approach [17, 18], deployment strategies and maturity of implementation will be performed within each of the four assessment protocols of the study.

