(2) Home hospitalization	(2.1) Assessment of hospital avoidance and early hospital discharge at district level	(2.1) Prospective controlled cohort study using PSM methods (2017–2018) (Additional file 2: Table S2)	(2.1) All patients admitted to the home hospitalization directly from the emergency room (*n* = 800 patients). Study of a deeply characterized subset (triple aim approach) of 200 patients. This subset will be used to generate (2.2).	(2.1) Patients admitted to conventional hospitalization directly from the emergency department of the same hospital (n = 800 patients). Study of a deeply characterized subset (triple aim approach) of 200 patients. This subset will be used to generate (2.2).	(2.1a) Health value generation of the service; expanded HDA using MCDA (n = 200). Factors modulating success of the implementation strategy.
		(2.2) Observational mixed-methods study combining network and cluster analyses with qualitative methodologies			
	(2.2) Recommendations for shared-care agreements between specialized and community-based care				
					(2.1b) KPI for service assessment
					(2.2) Strategies for enhanced interactions between specialized-community-based care.
(3) Prehabilitation	(3.1) Sustainability (cost-effectiveness of prehabilitation at HCB	(3.1) Prospective controlled cohort study using PSM methods (2016–2018) (Additional file 3: Table S3)	(3.1) All candidates for major surgery at HCB receiving prehabilitation (*n* = 500)	(3.1) Candidates for major surgery at HCB receiving usual care in the same hospital (*n* = 250)	(3.1a) Health value generation of prehabilitation at HCB
	(3.2) Recommendations for transition toward a regional peri-operative care program	(3.2) Randomized controlled trial to assess peri-operative care	(3.2) Candidates for major surgery at HCB receiving peri-operative care (*n* = 60)		(3.1b) KPI for service assessment
	(3.3) Enhanced pre-operative risk assessment	(3.3) Fixed cohort study	(3.3) All surgical patients in the last 5 years at HCB	(3.2) Candidates for major surgery at HCB receiving usual care (n = 60)	
					(3.2) Cost-effectiveness of peri-operative care and strategies for regional deployment.
					(3.3) Risk assessment tool for personalized prehabilitation

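### Protocol 3 matches on no calendar variable across 2016–2018, so a secular change in hospital stay would enter the prehabilitation estimate if the treated share rose over the window

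*Protocol article*

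**What the plan says.** The section on assessment protocol 3 describes a prospective controlled cohort at a single hospital. The intervention group is "500 consecutive patients undertaking prehabilitation, as the intervention group", compared at a "2:1 intervention to control ratio" with patients who have standard care before surgery. Table 1 describes the design as "Prospective controlled cohort study using PSM methods (2016–2018" (the bracket closes there). The Background gives another window: the three service protocols, prehabilitation among them, "address the deployment of specific IC services during the period 2017–2018".

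The aim is to evaluate "prehabilitation as a mainstream service in the ongoing deployment at HCB". The same section reports that in autumn 2017 "three multidisciplinary workshops using a design-thinking approach were carried out to refine the service workflow", and that the results fed the design of a later regional service.

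The groups are to be made comparable by propensity score matching on "type of surgery, age, sex, American Society of Anaesthesiologists index and GMA grading". The outcome is stated as follows: "The primary outcome will be cost-effectiveness, meaning reduced hospital stay and early re-admissions".

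**The concern.** Taking controls from the same hospital fixes the place of treatment but not its timing. Over a window of up to three calendar years, with a service still being deployed, the share of eligible patients who receive prehabilitation may rise. Usual-care patients would then lie earlier in the window than treated patients. The five matching variables describe the patient and the operation, so matching on them does not correct a difference in date.

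Hospital stay and re-admission can change over time for reasons unrelated to prehabilitation. If dates differ between the groups, that change becomes part of the estimated effect on the primary outcome. The unsettled window adds to this, because it leaves open when the run of 500 consecutive patients begins and which control period is meant.

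**Working it through.** **Reproducing the plan's figures.** The 2:1 ratio gives 500 / 2 = 250 controls, as in Table 1, and 500 + 250 = 750 in total. The surgery types sum to 525 + 30 + 30 + 165 = 750, so the counts agree. The article gives no effect size, standard deviation or power for protocol 3, so there is no further figure to reproduce.

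**How calendar time is handled in the four protocols.**
- Protocol 1: treated and control areas are compared year by year.
- Protocol 2: the intervention group comes from one year, October 2017 to October 2018.
- Protocol 4: one calendar year, 2018, with usual-care patients recruited during the study period.
- Protocol 3: 2016–2018 in Table 1, the longest window of the three service protocols, with no yearly comparison, no calendar matching variable and no statement on when controls are recruited.

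**Date gap between the groups (assumed pattern).** Let the treated share of the study sample change linearly from a to b over a window of L years, averaging 2/3 to agree with the 2:1 ratio. The mean surgery date is then L(1/2 + (b − a)/8) for treated patients and L(1/2 − (b − a)/4) for controls, so

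gap = (3/8) × L × (b − a).

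With L = 3:
- constant share of 67%: gap = 0
- 50% to 83%: (3/8) × 3 × 1/3 = 0.375 year
- 33% to 100%: (3/8) × 3 × 2/3 = 0.75 year, the extreme linear case

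**Spurious relative reduction in stay.** If stay falls by a fraction t a year for unrelated reasons, the apparent effect is 1 − (1 − t)^gap. Taking t = 3% and 8% (assumed; the documents give no trend):
- gap 0: 0%
- gap 0.375: 1 − 0.97^0.375 = 1.1%; 1 − 0.92^0.375 = 3.1%
- gap 0.75: 1 − 0.97^0.75 = 2.3%; 1 − 0.92^0.75 = 6.1%

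**Effect of the window.** With the two-year window in the Background, the extreme gap is (3/8) × 2 × 2/3 = 0.5 year and the reduction is 1 − 0.97^0.5 = 1.5% to 1 − 0.92^0.5 = 4.1%. The choice of window therefore affects the exposure to this bias.

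**The same in days (separate assumptions).** Let stay fall by 0.25 to 1.0 day a year, with a standard deviation of 5 to 10 days. At a gap of 0.75 year the spurious reduction is 0.19 to 0.75 day. The standard error is SD × sqrt(1/250 + 1/500) = 0.387 day at SD 5 and 0.775 day at SD 10. With no true effect, a two-sided 5% test then rejects in 5.7% of studies (0.25 day a year, SD 10) to 49% (1 day a year, SD 5). At a gap of 0 it rejects in 5%.

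**The case against.** The strongest reply is that no rising treated share is documented. The article calls prehabilitation a mainstream service and gives no uptake by year. With a constant share the gap and the bias are zero. The cohort is also prospective, in one hospital, with patients assessed before surgery on measures such as aerobic capacity and physical activity, which would be hard to collect from historical controls. This points to broadly concurrent controls and limits the likely size. It does not fix control dates or balance them within the window.

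A reader might infer from the autumn 2017 workshops that stay changed at that point, or that the effect must be reported before and after it. The text does not support this. It says the workflow was being refined and ties the results mainly to a future regional service. Even a real change in the workflow would be variation in the treatment, not a secular trend shared by treated and control patients. A before-and-after report would be a preference rather than a correction.

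A reader might also assume a gap of 0.5 to 1 year and conclude that bias is certain. That range leaves out zero, and its upper end exceeds the extreme linear case of 0.75 year.

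Additional file 3 is not shown and may state the timing of controls. The mismatch in windows is partly editorial, since the Background sentence covers three services at once. What stands is that the article lists its matching variables and calendar time is not among them.

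**Conclusion.** The point holds as a conditional one. Over a multi-year window with deployment under way, the stated matching set leaves calendar time uncontrolled, and the article does not require concurrent controls. If the treated share rose, a secular change in stay or re-admission would be counted as an effect of prehabilitation.

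The size cannot be found from the documents. It is 0% to about 6% of stay under two assumptions: a 3–8% yearly fall in stay, and a linear change in treated share giving a gap of 0 to 0.75 year. It may be small. The direction also depends on the assumptions: if stay rose over the period, or treated patients came earlier, the sign would reverse.

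The documents do not show that this bias is present. They show that the stated design does not guard against it, although a simple guard is available. The two windows, 2016–2018 and 2017–2018, contradict each other and need to be reconciled in any case.

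**What to change.** 1. Add year or a coarse period of surgery to the propensity score, and report its balance after matching alongside the five listed variables.
2. State that controls are drawn from the same accrual period as the treated patients.
3. Reconcile the window in the Background with that in Table 1, so that the start of the consecutive series is fixed.

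The cost is low. Date of surgery should already be in the hospital record, and a coarse period term may lose a few matches. With dates balanced, the gap is 0 and this source of bias disappears.

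Exact matching on half-year is not advised. Lung volume reduction and radical cystectomy have 30 patients each, so about 10 controls each if the 2:1 ratio holds within type. Six half-years would leave 10 / 6 = 1.7 controls per cell.
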